### Sample size

The required sample size was estimated to be 102 dyads, comprising 51 dyads per group (1:1 ratio), based on a repeated-measures design and two correlated means. The calculation was performed using an alpha level of 5% and a statistical power of 80%, adjusting for a 15% estimated attrition rate. The effect size data (MoCA: 0.7; MMSE 0.5) and the standard deviation of differences (MoCA: 1.8; MMSE 2.3) were derived from previous studies [61, 62]. All sample size calculations were executed using STATA-13 statistical software.

### Exploratory analysis: gut–brain axis and APOE genotype

To evaluate the biological plausibility of the INTERCOG intervention, an exploratory analysis of the gut–brain axis will be conducted on a targeted subsample of the first 40 participants (20 per group) diagnosed with amnestic mild cognitive impairment (aMCI). This phenotypic subset is analyzed not as a separate study, but as a mechanistic component intended to identify potential biological mediators that may underpin the clinical changes in cognitive function. Given that aMCI carries the highest risk of progression to Alzheimer’s disease and that the APOE-ε4 allele acts as a critical genetic moderator of neurodegeneration, characterizing these markers is essential to understanding the differential response to the multicomponent treatment.

To ensure the validity of the microbiota analysis and minimize confounding factors, specific exclusion criteria apply strictly to this subsample: (1) continuous use of probiotics, prebiotics, antibiotics, antifungals, or antivirals within the 3 months prior to enrollment; (2) a clinical diagnosis of inflammatory bowel diseases (such as Crohn’s disease or ulcerative colitis) or a history of surgical resection of the intestinal tract; and (3) the use of corticosteroids or immunosuppressants in the 30 days preceding the study. These microbiome-specific restrictions do not limit eligibility for the primary clinical trial, thereby preserving the representativeness of the main study sample.

For the statistical analysis of the microbiota data, alpha diversity differences will be evaluated via the Wilcoxon random-sum test, beta diversity variations will be assessed via permutational multivariate analysis of variance, and bacterial differences between the comparison groups will be identified via linear discriminant analysis effect size.

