In line with the above, and despite the scientific support for NPMIs, the need to determine their optimal combination and dosage persists. This underscores the importance of comprehensive and multicomponent interventions that integrate physical activity, rehabilitation or cognitive stimulation, and nutritional counseling, also involving the family member as a future caregiver and a key factor for adherence. Therefore, this study aims to evaluate the potential efficacy and feasibility of a multicomponent and transdisciplinary intervention directed at the family study partner–older adult dyad with MCI to optimize cognitive function. For this purpose, the efficacy of the NPMIs on global and domain-specific cognitive function in patients with MCI will be explored. Additionally, the feasibility, acceptability, and adherence to the intervention will be examined. Additionally, changes in the health-related quality of life of the dyad, social support, independence, frailty, physical capacity, family cohesion and adaptability, nutritional status, and, in a subgroup, potential changes in the composition of the gut microbiota will be evaluated.

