### Data collection procedures

Data collection will be conducted at three time points: (1) during the preselection process, (2) at baseline, and (3) during follow-up (at 3, 6, and 9 months of the study). At each point, a team of professionals from various previously trained disciplines will administer multiple questionnaires and perform measurements. The detailed schedules of the instruments, measurement time points, and evaluators are presented in Table 1.

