### Randomization and allocation concealment

A two-level stratified block randomization scheme will be employed to ensure balance across key demographic variables, given the characteristics of the screened population. The randomization sequence will be generated by a researcher independent of the core study team using the blockrand module (version 1.5) in R software (version 4.4.3). This individual will not participate in any study procedures.

The stratification process will include the following: first-level (stratification) dyads will be stratified into four groups based on two factors: sex (male/female) and age (above/below 71 years). Second level (block size): within each stratum, a block size of 2 is used to ensure an automatic 1:1 allocation ratio between the intervention and control groups.

The allocation sequence will be concealed, and the assignment will be executed in two phases: first, after the initial 52 dyads are completely identified and screened, and second, again for the remaining 50 dyads. This approach ensures that all participants maintain the same probability of assignment and helps maintain balance throughout the recruitment process. This entire procedure will be performed by personnel external to the core research team.

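### The microbiota exclusion bars only continuous antimicrobial use before enrolment, so a short antibiotic course shortly before the baseline stool sample is allowed (minor)

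*Protocol article*

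**What the plan says.** The section Exploratory analysis: gut–brain axis and APOE genotype restricts the microbiota work to the first 40 participants with amnestic MCI, 20 per group. It gives the purpose of the extra exclusions: "To ensure the validity of the microbiota analysis and minimize confounding factors, specific exclusion criteria apply strictly to this subsample".

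Two of the three exclusions concern drugs or supplements:

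- Criterion 1: "continuous use of probiotics, prebiotics, antibiotics, antifungals, or antivirals within the 3 months prior to enrollment".
- Criterion 3: "the use of corticosteroids or immunosuppressants in the 30 days preceding the study".

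The word continuous is not defined. The same section says that these restrictions do not affect entry to the main trial.

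The Background states the microbiota aim as a change: "in a subgroup, potential changes in the composition of the gut microbiota will be evaluated". Data collection procedures places the trial's follow-up visits at 3, 6 and 9 months. The article as shown does not say at which visits stool is collected.

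**The concern.** The plan itself treats antimicrobials as a threat to the microbiota comparison; that is why criterion 1 exists. Antibiotics are commonly taken in short courses, and a rule limited to continuous use does not, on its face, reach them. Criterion 3 shows that the authors could write an unqualified exclusion when they wanted one, so a reader will take the qualifier in criterion 1 as deliberate narrowing.

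There is also a limit on what the window can do. It ends at enrolment, whereas the outcome is a change and so needs at least one later sample. Antimicrobials taken between enrolment and that sample fall outside the rule.

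At stake is the precision and clarity of the diversity and composition comparisons. A few recently treated participants could widen the spread within arms or, by chance, fall mostly in one arm. In a component meant to look for biological mediators, that makes any difference harder to interpret.

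**Working it through.** The documents state no figure that depends on this criterion, so there is nothing to reproduce. The check is a reading of the text, followed by an illustration of scale.

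**Step 1. The two rules side by side**

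| | Criterion 1 | Criterion 3 |
|---|---|---|
| Agents | probiotics, prebiotics, antibiotics, antifungals, antivirals | corticosteroids, immunosuppressants |
| Use that excludes | continuous use only | any use |
| Window | 3 months | 30 days |
| Window ends at | enrolment | start of the study |

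**Step 2. Hypothetical cases**

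- A 7-day antibiotic course that ended one week before enrolment. It covers about 7/90 = 8% of a 3-month window, so it is not continuous use over that window. The participant is admitted.
- A 7-day corticosteroid course with the same timing. The participant is excluded under criterion 3.
- Daily antibiotic prophylaxis throughout the 3 months. The participant is excluded under criterion 1.
- An antibiotic course between enrolment and a later stool sample. It lies outside both windows.

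If continuous were instead taken to mean several consecutive days, the first case would be excluded. The text does not settle which reading applies, so two screeners could decide the same case differently.

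**Step 3. Scale (illustration)**

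Inputs: n = 40, with 20 per arm, from the section on the gut–brain axis. The proportion p with a short course in the window is assumed, because the documents give none. Participants are treated as independent.

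- Weight of one participant: 1/20 = 5% of an arm.
- Expected number exposed: 40 × p.
- Chance of at least one: 1 − (1 − p)^40. For p = 0.05 this is 1 − 0.95^40 = 0.871.
- Chance that the arms differ by 3 or more exposed participants: the sum of Bin(a; 20, p) × Bin(b; 20, p) over all a, b with |a − b| ≥ 3.

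| Assumed p | Expected exposed of 40 | At least one | Arms differ by ≥ 3 |
|---|---|---|---|
| 5% | 2 | 87% | 7% |
| 10% | 4 | 98.5% | 18% |
| 20% | 8 | > 99.9% | 32% |
| 30% | 12 | > 99.9% | 39% |

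At any of these rates, at least one exposed but eligible participant is likely. A marked imbalance between the arms is possible but is not the expected outcome.

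**The case against.** The strongest reply is that an exclusion criterion is applied at entry, so anchoring it to enrolment is normal, and no entry rule can exclude people for drugs they have yet to take. Sampling times and the handling of later exposure may sit in the full protocol or in Supplementary Table S3, neither of which is shown. The nursing assessment listed under Baseline and postintervention follow-up already includes a form with pharmacological history. All of this stands. It means that the anchor is not an error in itself and that the plan cannot be said to leave exposure unrecorded. What remains is narrower: the entry window as written cannot by itself protect a change outcome. The reply does not rescue the word continuous, which is in the stated text and works against the stated purpose.

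Three stronger readings are tempting, and the documents support none of them.

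- *Batch assignment stretches the gap by months.* Under Randomization and allocation concealment, the first assignment comes "after the initial 52 dyads are completely identified and screened". No recruitment rate is given, so the wait has no known length. It is also a wait before assignment, whereas the washout matters relative to the stool sample. If stool is taken with the baseline work-up, enrolment and first sample may be close together.
- *Antibiotic use will differ by arm.* One might infer this because only controls receive infection-prevention messages and only the intervention arm receives home visits. No passage or figure shows that either changes antibiotic use. Exposure before enrolment is balanced in expectation by randomisation.
- *Every endpoint of the substudy is affected.* APOE-ε4 frequency is also determined in this subsample, and antibiotics cannot change it.

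**Conclusion.** The concern holds as a minor defect of wording. Criterion 1, read plainly, admits participants with a recent short antimicrobial course, although the exclusions exist to keep such confounding out and criterion 3 beside it carries no such qualifier. The window also ends before the later sample that the change outcome implies.

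The consequence is added noise and possible chance imbalance in an exploratory comparison of 20 per arm. How much depends on the exposure rate, which is unknown here; the counts shown are illustrations over an assumed 5–30%. The conclusion rests on the ordinary meaning of continuous; if the authors meant a few consecutive days, or meant the word only for probiotics and prebiotics, the text needs to say so. The feasibility outcomes, the cognitive analysis, APOE and entry to the main trial are untouched.

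**What to change.** 1. Reword criterion 1 so that any use of antibiotics, antifungals or antivirals in the 3 months before enrolment excludes from the subsample. Keep continuous for probiotics and prebiotics if that was the intention, and define it. State which routes of administration count.
2. Use the pharmacological history on the nursing form to record antimicrobial exposure, with dates, before each stool sample.
3. Pre-state a sensitivity analysis of the diversity and composition comparisons that leaves out exposed samples. This also covers anyone already enrolled under the present wording: the registration entry says that the trial is recruiting, and Ethics and dissemination describes substudy consent in the past tense.

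The cost is one reworded criterion, one exposure item per sampling visit and one extra run of analyses already planned. The downside is a few more substudy screen failures or flagged samples. Main-trial eligibility does not change.

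### The microbiota substudy's named tests compare the arms only; with no stated baseline, cognition or APOE term, they do not reach the aims of mediators and differential response

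*Protocol article*

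**What the plan says.** The aims appear in two places. The Background says that "in a subgroup, potential changes in the composition of the gut microbiota will be evaluated". The section on the gut–brain axis and APOE genotype describes the subsample (the first 40 participants with amnestic MCI, 20 per group) as "a mechanistic component intended to identify potential biological mediators that may underpin the clinical changes in cognitive function". After calling APOE-ε4 a genetic moderator, it adds that "characterizing these markers is essential to understanding the differential response to the multicomponent treatment".

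The methods appear once, at the end of that section. The first is "alpha diversity differences will be evaluated via the Wilcoxon random-sum test", where the printed name can only mean the rank-sum test. The second is "beta diversity variations will be assessed via permutational multivariate analysis of variance". The third is "bacterial differences between the comparison groups will be identified via linear discriminant analysis effect size".

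The only longitudinal model in the article is the mixed model under Statistical methods. It has group, time and their interaction, a participant random effect, and perceived social support as a time-varying covariate. It names no microbiota measure, mediator or APOE term. The Abstract is more modest than the section itself: it says only that microbiota diversity will be characterised and APOE-ε4 frequency determined.

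**The concern.** The stated purpose and the listed analyses do not match. A mediator question needs the marker related to the cognitive outcome. A differential-response question needs a marker-by-arm term in a model of that outcome. Neither appears among the methods assigned to these data.

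A question about change needs each person's baseline to enter the analysis, and no method is stated to use it. With 20 people per arm, baseline is the cheapest source of precision available.

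If the plan stays as it is, one of two things is likely. Mechanistic statements will be drawn from arm differences in microbiota alone, or the models linking microbiota or APOE to cognition will be devised after the data are seen.

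**Working it through.** **Step 1: aims against methods.** The article states no power or effect size for the subsample, so there is no figure of its own to reproduce.

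| Stated aim | What an analysis of it needs | What the named methods contain |
|---|---|---|
| Changes in microbiota | Baseline and follow-up for each person | Between-group tests; no baseline, time or participant term stated |
| Potential mediators of cognitive change | Marker related to cognition | No cognitive variable |
| Differential response, APOE as moderator | Marker-by-arm term on a cognitive outcome | No APOE term, no cognitive variable |

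The second and third rows hold whatever the sampling schedule is. The first depends on how the tests are applied, which the text does not say.

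**Step 2: what leaving out baseline costs for alpha diversity.**

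Inputs:
- 20 per arm (substudy section) and alpha 0.05 (Statistical methods).
- Assumed here: two-sided testing, 80% power for the substudy, approximately normal data, and a baseline to follow-up correlation r of 0.3 to 0.8. The article gives no correlation.

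Unadjusted detectable difference:
- Two-sample t-test, 20 per arm, 80% power: d = 0.909 SD.
- Rank-sum, with asymptotic relative efficiency 3/π = 0.955: 0.909 / √0.955 = 0.930 SD.

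Baseline-adjusted (ANCOVA) detectable difference, 0.909 × √(1 − r²):

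| Assumed r | Variance removed (r²) | Detectable difference |
|---|---|---|
| 0.3 | 9% | 0.909 × 0.954 = 0.867 SD |
| 0.5 | 25% | 0.909 × 0.866 = 0.787 SD |
| 0.7 | 49% | 0.909 × 0.714 = 0.649 SD |
| 0.8 | 64% | 0.909 × 0.600 = 0.545 SD |

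The plain normal approximation, (1.960 + 0.842) × √(2/20), gives slightly smaller values: 0.886 SD for the t-test, 0.907 SD for the rank-sum, and 0.845 to 0.532 SD adjusted over the same correlations. The picture is the same.

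**Step 3: simulation.** 4,000 replicates, 20 per arm, normal data.

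| Assumed r | Rank-sum on follow-up: type I error | Rank-sum on follow-up: power at 0.8 SD | Rank-sum on change scores: power at 0.8 SD | ANCOVA: power at 0.8 SD |
|---|---|---|---|---|
| 0.3 | 5.1% | 66% | 52% | 72% |
| 0.5 | 4.1% | 67% | 67% | 81% |
| 0.7 | 4.8% | 66% | 87% | 92% |

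The follow-up comparison keeps its error rate, so what is lost is precision. Change scores are no safe substitute, because at r = 0.3 they do worse than ignoring baseline.

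**The case against.** The section is headed as exploratory and speaks of potential mediators. Testing whether the intervention shifts the microbiota is a legitimate first step towards candidate mediators. The sentence on differential response can be read as rationale and not as a commitment to a treatment-by-APOE test. Sampling times and model details may sit in a supplement or a fuller plan, and their absence from an article is no fault. These points stand, and they keep the matter to the substudy and to wording and analysis choice.

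Three stronger readings are tempting, and the document does not support them:
- **That the tests cannot assess change at all.** The text does not say which values enter. A rank-sum test can be run on within-person change, and PERMANOVA can take covariates and restricted permutations. Baseline is not stated as used, which is different from being excluded. Even on follow-up values alone, the randomised comparison validly tests for an intervention effect.
- **That the p values will be wrong because repeat samples from one person are treated as independent.** Nothing in the article says that samples will be pooled in this way.
- **That much of the precision is wasted.** This depends on a correlation the article does not give. At r = 0.3 the gain is small (0.91 to 0.87 SD), and the calculation covers one scalar measure, not PERMANOVA or LEfSe.

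The objection does not remove the mismatch on cognition and APOE. The article assigns these data their own named methods and does not defer to another document for them. No sampling schedule would put a cognitive outcome or an APOE term into those tests.

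**Conclusion.** The concern holds in a limited form. As listed, the substudy analyses can show at most whether the arms differ in microbiota. They do not address mediation or differential response. They are valid under randomisation but less precise than a baseline-adjusted analysis: about 0.91 to 0.93 SD detectable unadjusted, against about 0.87 SD (r = 0.3) to 0.55 SD (r = 0.8) adjusted.

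Those figures rest on 20 analysable people per arm, 80% power, two-sided 5%, roughly normal data and an assumed correlation. The recommendation to adjust also rests on baseline samples being taken, which the Background's reference to changes implies but the article does not confirm. The mismatch on cognition and APOE rests on none of these. The point is worth correcting because the change is cheap, and it has no bearing on the feasibility outcomes or the main cognitive analysis.

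**What to change.** If baseline and follow-up samples are taken:
1. Analyse follow-up alpha diversity by ANCOVA on arm and baseline diversity, rank-transformed if skewed, in place of the unadjusted rank-sum test.
2. Run PERMANOVA with arm, time and arm × time, using permutations that respect the participant.
3. Add one exploratory regression of follow-up MoCA on change in diversity, adjusted for arm and baseline MoCA. Report it with a 95% CI as an association. In 40 people it does not establish mediation and should not be described as doing so.

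In either case:
4. Limit APOE to describing allele frequency, as the Abstract already does, and remove the differential-response claim.
5. Reword mediators as candidate markers associated with cognitive change.

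If only one sample per person is taken, steps 1 to 3 do not apply as written, and the Background's reference to changes in composition should also be deleted.

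The cost is a little extra analysis and more modest claims. No further participants are needed, and no samples beyond those the stated aims already imply.

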### Randomization and allocation concealment

A two-level stratified block randomization scheme will be employed to ensure balance across key demographic variables, given the characteristics of the screened population. The randomization sequence will be generated by a researcher independent of the core study team using the blockrand module (version 1.5) in R software (version 4.4.3). This individual will not participate in any study procedures.

The stratification process will include the following: first-level (stratification) dyads will be stratified into four groups based on two factors: sex (male/female) and age (above/below 71 years). Second level (block size): within each stratum, a block size of 2 is used to ensure an automatic 1:1 allocation ratio between the intervention and control groups.

The allocation sequence will be concealed, and the assignment will be executed in two phases: first, after the initial 52 dyads are completely identified and screened, and second, again for the remaining 50 dyads. This approach ensures that all participants maintain the same probability of assignment and helps maintain balance throughout the recruitment process. This entire procedure will be performed by personnel external to the core research team.

### Blinding

Owing to the nature of the intervention, which cannot be masked with a placebo, it is not possible to blind the participants, their family members, or the intervention team. However, to minimize detection and performance bias, blinding will be strictly maintained at the assessment and analytical levels. The assessment team and data collectors will remain operationally independent from the intervention staff throughout the study. Furthermore, participants will be requested at each follow-up visit to refrain from discussing their assigned activities with the evaluators. Finally, statistical analysis will be performed by an analyst blinded to group allocation; data will be managed using arbitrary codes, which will only be unmasked upon completion of the primary analysis.

### Statistical methods

Continuous data will be described using means and standard deviations (SDs) or medians and interquartile ranges (IQRs), depending on their distribution as assessed by the Shapiro–Wilk test. These data will be compared between the intervention and control groups via Student’s *t*-test or the Mann–Whitney *U* test, respectively. Categorical data will be summarized using absolute and relative frequencies and compared between groups via the *χ*^2^ test or Fisher’s exact test, as appropriate.

Outcomes will be analyzed across the baseline, 3-, 6-, and 9-month follow-up measurements via generalized linear mixed-effects models (GLMMs). These models will include fixed factors (intervention group, time, and the group × time interaction) and a random effect for participants to account for individual variability. The models utilize maximum likelihood estimation (MLE) methods to handle data that are missing at random (MAR). Potential confounding variables identified during the descriptive analysis were adjusted for. To account for the potential confounding effect of social interaction, perceived social support (measured via the MOS survey) will be included as a time-varying covariate in the models. The results are reported as adjusted mean differences with their respective 95% confidence intervals (95% CIs). Imputation methods will not be used.

Analysis will be performed on both an intention-to-treat (ITT) and per-protocol (PP) basis. To account for multiplicity and reduce the risk of type I error across the various secondary outcomes, *p *values will be adjusted using the Benjamini–Hochberg false discovery rate (FDR) procedure. The level of statistical significance will be set at *α* = 0.05. All statistical analyses will be conducted via STATA 17 (Stata Corporation, College Station, USA).

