## Abstract

**Background:**

Given the risk of progression to dementia ranging from 6 to 44.8% over approximately 4 years of follow-up, nonpharmacological multicomponent interventions are emerging as promising strategies to improve or maintain cognitive function and quality of life in individuals with mild cognitive impairment (MCI). This pilot study aims to evaluate the feasibility and potential efficacy of a multicomponent and transdisciplinary intervention focused on the dyad of older adults with MCI–family study partner to promote cognitive function in older adults.

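### One random effect per participant forces equal correlation between all visits; if correlation falls with time, visit-specific standard errors are too small at 9 months and too large at 3 months

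*Protocol article*

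**What the plan says.** The Statistical methods section sets out one model for the outcomes generally: "Outcomes will be analyzed across the baseline, 3-, 6-, and 9-month follow-up measurements via generalized linear mixed-effects models (GLMMs"). The fixed part is given as "These models will include fixed factors (intervention group, time, and the group × time interaction"), so visit enters as a factor. The random part is one term, "and a random effect for participants to account for individual variability". Estimation is by maximum likelihood, results are adjusted mean differences with 95% confidence intervals, and "The level of statistical significance will be set at" 0.05. The section names no random slope, residual covariance structure or robust standard error.

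The Sample size section gives 51 dyads per group, 15% attrition, and a standard deviation of differences of 1.8 for the MoCA and 2.3 for the MMSE. It gives no visit-level standard deviation and no between-visit correlation, and does not say over which interval those differences were taken.

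The Outcomes section makes feasibility, acceptability and adherence primary and cognition exploratory.

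**The concern.** With a continuous score, one random effect per participant and independent residuals give compound symmetry. The variance of change from baseline is then the same at 3, 6 and 9 months, and the model estimates it as a single pooled quantity.

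That is doubtful in this population. The abstract speaks of progression risk "Given the risk of progression to dementia ranging from 6 to 44.8% over approximately 4 years of follow-up", the Background section gives higher hazards with diabetes and cardiac disease, and the section on the exploratory gut–brain analysis anticipates a differential response to treatment. If participants change at different rates, or if scores drift, the 0–9-month correlation falls below the 0–3-month correlation. The true variance of change then grows with time while the model holds it constant.

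The pooled value is too large at 3 months, when the 12-week programme ends, and too small at 9 months, when maintenance is judged. Intervals are too wide at the first and too narrow at the second. The same sentence governs the secondary outcomes, so any visit-specific p values entered into the Benjamini–Hochberg step would carry the error with them.

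**Working it through.** **Inputs.** From the Statistical methods section: four visits, the model above and α = 0.05 (sidedness not stated; taken as two-sided). From the Sample size section: "The required sample size was estimated to be 102 dyads, comprising 51 dyads per group (1:1 ratio"). Assumed: the between-visit correlations, since the article gives none, and equal variance of 1 at each visit.

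**Formulas** (complete data, no treatment effect)
- Model-based variance of change, up to a common factor: M = 2 × (mean variance − mean covariance over the six visit pairs).
- True variance of change to visit k, up to the same factor: T_k = Var(Y_k) + Var(Y_0) − 2 Cov(Y_0, Y_k).
- Actual size = 2 Φ(−1.96 √(M / T_k)).
- The group size cancels, so these sizes do not depend on 51 per arm.

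**The plan's own figure.** With equal correlation, say 0.80 throughout, M = 2 × (1 − 0.80) = 0.40 and T_k = 0.40 at every visit. The ratio is 1 and the size is exactly 5%. The stated 0.05 is correct under that condition.

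**One case in full: AR(1) with correlation 0.7**
- Correlations at lags of 3, 6 and 9 months are 0.70, 0.49 and 0.343.
- The six pairs comprise three at lag 3, two at lag 6 and one at lag 9, so mean covariance = (3 × 0.70 + 2 × 0.49 + 0.343) / 6 = 0.5705.
- M = 2 × (1 − 0.5705) = 0.859.
- 3 months: T = 2 × (1 − 0.70) = 0.600; M/T = 1.43; standard error 20% too large; size 1.9%.
- 9 months: T = 2 × (1 − 0.343) = 1.314; M/T = 0.654; standard error 19% too small; size 11.3%.

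**Range**

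| Correlation at lags 3 / 6 / 9 months | Size at 3 months | Size at 9 months | Joint 3-df group × time test |
|---|---|---|---|
| 0.80 / 0.80 / 0.80 | 5.0% | 5.0% | 5.0% |
| 0.84 / 0.83 / 0.82 | 4.5% | 5.9% | 5.0% |
| 0.80 / 0.78 / 0.76 | 4.3% | 6.5% | 5.0% |
| 0.82 / 0.79 / 0.76 | 3.9% | 7.4% | 5.2% |
| 0.80 / 0.75 / 0.70 | 3.4% | 8.4% | 5.3% |
| AR(1) 0.5 | 2.6% | 9.2% | 5.7% |
| AR(1) 0.7 | 1.9% | 11.3% | 6.3% |
| AR(1) 0.9 | 1.4% | 13.4% | 6.9% |

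**Simulation check** (51 per arm, random-intercept ML fit, 2,500 trials per case; sizes at 3 / 6 / 9 months)
- AR(1) 0.7: 2.5 / 8.0 / 12.2% without dropout; 1.6 / 7.3 / 12.7% with 15% random dropout.
- Equal correlation 0.7: 4.9 / 5.6 / 5.1% without dropout; 5.4 / 5.0 / 5.3% with 15% dropout.

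A separate simulation (2,000 trials per case, 15% random dropout) fitted an unstructured covariance and gave 4.2–6.0% at 3 and 9 months.

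**The case against.** **The size is not known.** A reader might infer that the 9-month test rejects a true null about twice as often as stated. The article does not support that as a fact, because it gives no correlation and the answer runs from 1.0 to about 2.7 times nominal. Its progression figures point to the lower part. At a constant hazard, 6% and 44.8% over 3.7 years become 1 − 0.94^(0.75/3.7) = 1.2% and 1 − 0.552^(0.75/3.7) = 11.3% over 9 months. Suppose progressors lose 2–3 extra MoCA points linearly by 9 months and everyone else's change has SD 1.8. The 9-month size is then 5.1–5.2% at the low rate and 5.9–6.9% at the high rate; 5 extra points at the high rate are needed to reach 9.5%. This stands. Progression to dementia is only one source of decay, but the size must be stated conditionally.

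**The overall interaction test is nearly sound.** Correct. The plan singles out no 9-month contrast, and the joint test stays at about 5–7%. The point concerns visit-specific differences and their intervals.

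**Missing data.** The section says "The models utilize maximum likelihood estimation (MLE) methods to handle data that are missing at random (MAR"), and a reader might infer that the restricted covariance biases the estimates under dropout. No such bias has been shown: the simulations used random dropout only, and size stayed near 5% under equal correlation.

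**This is detail for an analysis plan.** A fuller plan may name a residual structure or robust standard errors, and the published phrase does not exclude them. But the article does not leave the random part open. It states one, and that one is restrictive for these data.

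**The outcomes are exploratory.** This limits the consequence. The section on data collection at baseline and follow-up does call the neuropsychological tests primary, against the Outcomes section. Either way, the criteria under Feasibility analysis and success thresholds do not use this model.

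**Conclusion.** The point holds conditionally. For continuous outcomes, the stated model gives correct visit-specific inference only if the variance of change from baseline is the same at every visit. If correlation falls with time apart, the 9-month contrast rejects too often (about 6–9% under mild decay, about 9–13% under AR(1)-type decay with lag-3-month correlation 0.5 to 0.9) and the 3-month contrast too seldom (down to 1.4%). With no decay there is no error.

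The direction follows from the model. The size rests on assumed correlations, equal visit variances and two-sided testing. The consequence is confined to visit-specific p values and 95% confidence intervals of the exploratory cognitive and the secondary outcomes; the joint interaction test is little affected and the feasibility decision not at all. It is worth correcting before analysis, but it does not undermine the trial.

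**What to change.** For continuous outcomes, replace the single participant random effect with an unstructured within-participant covariance over the four visits. Keep visit categorical, and fit by REML with Kenward–Roger degrees of freedom. Stata 17, already named in the plan, does this with `mixed`, using `noconstant residuals(unstructured, t(visit)) reml dfmethod(kroger)`. State the fallback in advance: if the model does not converge, use a simpler non-exchangeable structure, or a random intercept with robust standard errors. Non-continuous outcomes can stay with the generalized linear mixed model.

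The cost is one sentence and a changed model option. There are ten covariance parameters (four variances and six covariances) instead of two, which is manageable with 102 participants and four visits and costs little precision if correlation turns out not to decay. No new data or visits are needed.
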